### Monitoring

A Data Safety and Monitoring Board (DSMB), whose members will be independent of the funding agency, the National Institute on Drug Abuse (NIDA), will be brought together to oversee the study’s activities and to ensure the safety of human subjects, validity of findings, and need for further data collection. The study principal investigator (PI), [name], will interact with the DSMB at the DSMB’s discretion (at least two meetings per year), providing them with material to review, monitor, evaluate, audit, and make recommendations regarding: (1) protocols, informed consent procedures, and safety plans; (2) study progress (i.e., recruitment and retention, risk/benefit ratio for subjects, adherence to timetable, quality of data); (3) the impact of new treatment developments on the risk/benefit ratio of the study; (4) continuation, modification, or termination of ongoing studies based on adverse events or beneficial outcomes; (5) interim analyses; (6) confidentiality of trial data and results of monitoring; and (7) procedures likely to increase subjects’ burden, to raise ethical concerns, or to give the appearance of a conflict of interest.

The PI will make the following available to the DSMB: (1) all adverse events (RTI International protocol requires the reporting, in writing, of all adverse events within 5 days of the study team becoming aware of the adverse event. All adverse event forms will be made available to the DSMB as well as tables summarizing the occurrence of specific events.); (2) all interim data analyses; (3) analyses requested by the DSMB; and (4) all reports to NIDA and all publications. Finally, data management procedures, including those for data entry and quality checks, coding, security, and storage are available from the study PI.

### Power analyses

The proposed study will have a small, but appropriate [65] sample size of 60. This study is developmental in nature, which informs how we have chosen to address the choice of error rates and power to detect effects in our clinical and public health outcomes. Prior research suggests small to medium substance use and psychiatric symptom effects of DDMI [25, 27] and IGT [28–30]. Therefore, type I error rate α = 0.15 was chosen so as not to limit power to conduct inferential analyses, giving an 80% chance (1 – β = .80) to detect a difference between the treatment conditions that would explain 9% of the total variance [θ^2^ = .09] in an outcome variable if the null hypothesis were false (calculated using G*Power 3.1 [66]). This approach allows for increased opportunity to detect a smaller effect, while running the risk that the effect will not replicate. This course of action is appropriate for a developmental study and is consistent with prior research involving adults with SMI and preliminary-stage multivariable models [61].

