To address Aims 2.1 and 2.2 regarding the feasibility and acceptability of and fidelity to the treatment and protocols, we will integrate qualitative and quantitative data by transforming qualitative data (e.g., noting the occurrence of themes in interviews and focus groups) to support or refute quantitative results (i.e., data merging) [51–53]. All qualitative data collected from inmates, clinicians, and jail personnel will be analyzed using the coding approach described above for Aim 1. Feasibility will be evidenced by the acceptable rates of participant exposure (85% complete DDMI; attend >1 IGT session/week) and retention (>75% completion rate) in the treatment continuum [54–56]. Acceptability to clinicians will be evidenced by focus group and interview themes reflecting an overall more positive than negative perception (e.g., endorsement for continuing the program, even if minor inconveniences are noted). Acceptability to inmates will be evidenced by average CSQ-8 item scores >3 [57] and interview themes reflecting more positive than negative perceptions. Fidelity will be evidenced by mean item scores >4 (Moyers, Martin, Manuel, Miller, Ernst. Revised global scales:motivational interviewing treatment integrity 3.1. 1 (MITI 3.1. 1). Unpublished) for the DDMI and >3 [28] for the IGT fidelity ratings.

We will use a generalized linear mixed model (GLMM) to address Aim 2.3 regarding the effectiveness of the DDMI-IGT treatment condition. In addition to inferential tests of significance and associated confidence intervals, effect sizes will be estimated. Our approach will be extended to estimate standardized differences between the means for planned contrasts in the amount of change that has taken place between pairs of times. Effect sizes will be ranked from highest to lowest, tabled, and graphed. Mindful of concerns regarding estimation of effect sizes in pilot studies and the accuracy of estimates of replication, our goal will be to identify a consistent pattern in the results that will help determine the choice of primary outcome measures in future research [58, 59].

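### The power statement pairs 80% with 9% of total variance, but at N = 60 and alpha 0.15 the two do not match: 9% gives about 83.5% power, and 80% belongs to about 8.1%

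*Protocol article*

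**What the plan says.** The Power analyses section of the protocol article gives a "small, but appropriate [65] sample size of 60". It then says that "type I error rate α = 0.15 was chosen so as not to limit power to conduct inferential analyses", and that the result is 80% power "to detect a difference between the treatment conditions that would explain 9% of the total variance". The effect size carries a symbol: "explain 9% of the total variance [θ^2^ = .09] in an outcome variable". The symbol is not defined in the article. G*Power 3.1 is named as the software.

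The same section justifies the relaxed alpha by the developmental nature of the study and accepts openly that an effect found this way may not replicate. It mentions no loss to follow-up. The subsection on the pilot randomized trial, under participant identification and recruitment, describes random assignment to two conditions and gives no allocation ratio.

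**The concern.** A power statement fixes four linked quantities: sample size, alpha, effect size and power. Given any three, the fourth follows. Here all four are stated, so they can be checked against each other, and as worded they disagree.

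The likely source of trouble is that two effect-size measures have similar values in this range. The share of total variance explained (R², or eta-squared) divides the between-group variance by the total. Cohen's f² divides it by the residual variance. At 0.09 they differ by under one percentage point, enough to move power by about three points.

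Little is at stake for this pilot. But this is the only detectable effect that the article gives, and someone reading or reusing it cannot tell which measure the 0.09 is.

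**Working it through.** **Inputs.** From Power analyses: N = 60, alpha = 0.15, power = 0.80, effect = 0.09. From the recruitment section: two conditions, hence one numerator degree of freedom. Assumed because the article does not say: two-sided testing, 30 per arm, all 60 analysed as independent observations.

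**Method.** Noncentral F test with 1 and N − 2 = 58 degrees of freedom and noncentrality λ = N × f², where f² = R²/(1 − R²). With equal arms d = 2√f². This is equivalent to the two-sided two-sample t test.

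**1. The reading that reproduces the stated 80%.** Take .09 as f².
- λ = 60 × 0.09 = 5.40; power = 80.6%.
- f = 0.30, d = 0.60.
- Share of total variance = 0.09/1.09 = 0.0826, or 8.3%.

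**2. The sentence as worded.** Take .09 as the share of total variance.
- f² = 0.09/0.91 = 0.0989; d = 2√0.0989 = 0.629.
- λ = 60 × 0.0989 = 5.93; power = 83.5% (normal approximation 84.0%).

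**3. The effect that belongs to 80%.** Solve for power 0.80 at N = 60.
- f² = 0.0883, which rounds to .09; d = 0.594.
- Share of total variance = 0.0883/1.0883 = 0.081, or 8.1% (normal approximation 8.0%).

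**4. Does an unstated assumption restore 80% at 9%?**

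| Variant, 9% of variance unless noted | Power |
|---|---|
| One-sided alpha 0.15 | 91.7% |
| 1 to 15 covariates (loss of residual df only) | 83.5% to 83.3% |
| 2 or 3 numerator df | 75.4% or 69.6% |
| Correlation test, r = 0.30, Fisher z | 81.5% |
| Correlation test, r = 0.30, exact, simulated | 82.2% |
| 20:40 split with d held at 0.629 | 79.9% |
| 54 analysed (10% loss) | 80.2% |
| 53 analysed | 79.6% |
| 45 analysed (25% loss) | 74.1% |

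The correlation rows treat the comparison as one between two normal variables, which a two-arm contrast is not. The 20:40 row does not keep 9% of variance: the factor 20 × 40/60² = 0.222, times 0.629² = 0.396, gives f² = 0.088, and 0.088/1.088 = 0.081. It is the 8.1% of step 3 again. Only the row with 54 analysed keeps both the 9% and the 80%, and the article states no such allowance.

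**The case against.** The best case for the text is that the calculation was probably sound and only its description slipped. With f² = 0.09 power is 80.6%, and solving for the detectable effect gives f² = 0.088, which rounds to .09. The symbol may itself be a typesetting or conversion fault. An article also condenses a fuller protocol, so an allowance for about 10% loss, which would make 80% right at 9%, could sit in a document not shown. And since power for 9% with all 60 analysed is above 80%, the statement is true as a lower bound.

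Much of this stands. The stated power is not shown to have been miscalculated, and the article need not name the G*Power module or the sidedness. What does not stand is the sentence as worded. The f² reading rescues the number by replacing the measure that the sentence names. The loss reading needs an analysed number other than the 60 to which the section ties the figure.

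Three stronger readings are tempting, and the documents do not support them:

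- *Alpha is larger than it needs to be.* With 60 analysed and 9% of variance, alpha of about 0.117 would already give 80%. But the section rests its choice on the developmental nature of the study and does not present 0.15 as the smallest alpha that meets a target. The surplus also disappears with 54 analysed.
- *N = 60 rests on a faulty calculation.* The section calls 60 appropriate on the strength of a cited source and then gives the power that results. It does not show that 60 was derived from this calculation.
- *The detectable effect is simply wrong.* It is right for f² and does not match for share of variance. The article does not settle which was meant.

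**Conclusion.** The point holds as a minor mismatch in a stated figure. With 60 analysed, two arms of 30 and a two-sided test at 0.15, a difference explaining 9% of total variance has about 83.5% power, not 80%, and 80% power corresponds to about 8.1% of variance. The gap is 3.5 points of power, or 0.7 to 0.9 points of variance (8.3% or 8.1% against 9%). It is conservative. That an f² value was described as a share of variance is the likeliest explanation, but it is an inference.

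The result rests on two-sided testing and on all 60 being analysed as independent observations. Nothing here calls for a different sample size, alpha or conduct.

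**What to change.** Rewrite the one sentence so that its figures agree. Either of these would do:

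- *80% power for f² = 0.09, about 8% of total variance*; or
- *about 83.5% power for a difference explaining 9% of total variance*.

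Replace the undefined symbol next to .09 with the measure that was used. If 80% at 9% was meant to allow for loss to follow-up, say so and state the analysed number to which it applies, about 54.

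The cost is one sentence in the power section, with no change to the sample size, the alpha or the running of the trial.

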## Discussion

Adults with mental illness suffer disproportionately from drug and alcohol problems and are overrepresented in jails. Our study aims to address the problem of limited treatment for this population. Therefore, we will adapt DDMI and IGT for jail inmates with CODs and evaluate the acceptability, feasibility, fidelity, and effectiveness of implementing the adapted treatment continuum and associated research and communication protocols.

### Innovation

Our study will advance current research and practice regarding evidence-based treatment for inmates with CODs and associated research methodologies. We will adapt two interventions, DDMI and IGT, for justice-involved adults with CODs. Our project is grounded in evidence-based conceptual and treatment processes and will have the potential to improve substance use, psychiatric, arrest, and routine outpatient treatment uptake outcomes among an underserved and high-risk population. This type of research is needed to address the increasing rates of persons with CODs in jail populations and associated treatment failure. Second, the development and implementation of RCT methodologies is needed within and across jail and community settings to demonstrate the feasibility, acceptability, and effectiveness of adapting treatments and conducting RCTs with this population. Accordingly, this study may influence the progression of subsequent CODs and jail research and encourage others to adopt similar rigorous and system-bridging approaches.

### Limitations

Our study has several limitations in the design and implementation. Although court orders can be successful in increasing treatment participation among adults with CODs, substance use disorders (SUDs), and SMIs [67–69], we do not propose any judicial oversight. This decision is in line with the preferences of our community partners and other ongoing studies [70] and has proven to be successful in retaining participants. Given our focus on one jail, the generalizability of our findings may be limited; however, generalizability of our findings can be examined in a future full-scale RCT. Allowing access to TAU in both experimental conditions also presents several potential limitations. As much as possible, our community agencies will have different clinicians deliver the DDMI-IGT and usual care services to experimental and control participants; however, DDMI-IGT and usual care will be provided in the same agencies, which may result in treatment contamination. Fidelity assessments will allow us to monitor DDMI-IGT treatment integrity and to address this potential contamination. It also is likely that, across both experimental conditions, inmates will receive different types and intensities of usual care services, resulting in treatment heterogeneity. This will not affect study interpretability, however, because service intensity will be titrated to individual client needs, consistent with the RNR framework [39]. If our DDMI-IGT continuum increases the amount or duration of usual care service uptake, the extent to which improvements in outcomes can be “explained” by amount or duration of usual care services could be explored by statistically controlling for these services and comparing the treatment conditions, e.g., through analysis of covariance (ANCOVA) models. Lastly, given that our study is focused on the preliminary treatment adaptations and feasibility, we have not focused on differential effects of DDMI and IGT within our treatment continuum.

### Trial status

Participant recruitment for the RCT is ongoing.

## Abbreviations

BJMHS: Brief Jail Mental Health Screen
CODs: Co-occurring mental and substance use disorders
DDMI: Dual-diagnosis motivational interviewing
EB-IIM: Evidence-Based Interagency Implementation Model
IDDT: Integrated dual disorder treatment
IGT: Integrated group therapy
NIC: National Institute of Corrections
NOS: Not otherwise specified
RCT: Randomized controlled trial
RNR: Risk-Need-Responsivity
SMI: Serious mental illness
TAU: Treatment as usual.
